**15.1. Definition of Adverse Event**

- “Adverse Event (AE)” refers to any undesirable and unintended signs (signs, e.g., abnormalities in laboratory test values), symptoms, and diseases occurring in subjects during clinical trials, and it does not necessarily have to have a causal relationship with the investigational medical device.

- - “Adverse Device Effect (ADE)” refers to any harmful and unintended reaction caused by an investigational medical device, and a causal relationship with the investigational medical device cannot be excluded.
- “Unexpected Adverse Device Effect” refers to a difference in the aspect of an adverse medical device reaction or the degree of harm in light of available medical device-related information (For example, from that of Investigator’s Brochure or attachments of medical device).

**15.2. Definition of Serious Adverse Events/Adverse Medical Device Reactions**

Serious adverse event/Adverse medical device reaction refers to a case that falls under the following among the adverse reactions caused by medical devices used in clinical trials.

① Results in death or is life-threatening

② Requires hospitalization or prolongation of existing hospitalization

③ Results in persistent or significant disability or impairment

④ Results in congenital malformation or anomaly

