**12.3.2. Assessment Criteria and Assessment Method**

In this clinical trial, adverse events are all undesirable medical findings that cause symptoms not observed before the start of the clinical trial are classified as adverse events. In accordance with the definitions and criteria described in the section ‘15. Assessment Criteria, Assessment Method and Reporting of Safety Including Side Effects’, expected side effects are also classified as adverse events. The severity of adverse events is classified into mild, moderate, and severe, and the use of terms is based on MedDRA’s ‘Preferred term’ and ‘System organ class’.

1. **Data Collection and Statistical Analysis**

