**15.4. Adverse Events Assessment Criteria**

In this clinical trial, adverse events are all undesirable medical findings that cause symptoms not observed before the start of the clinical trial are classified as adverse events. Expected side effects are also classified as adverse events, and the severity of adverse reactions is classified into mild, moderate, and severe, and they are reported using the ‘Preferred term’ and ‘System organ class’ of MedDRA.

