**15.5. Expected Adverse Events and Precautions**

**15.5.1. Expected Adverse Events**

- Pain
- Nausea
- Vomiting
- Abdominal tenderness
- Edema
- Abdominal cramping
- 1-3 degree burns
- Internal tissue thermal damage
- Leg and hip pain
- Vaginal bleeding more than before treatment
- Sciatic nerve injury
- Abdominal and pelvic organ damage (bladder, uterus, intestine, etc.)
- Pain that does not respond to drugs
- Urinary tract infection
- Urination disorders
- Fever due to infection
- Hypersensitivity reactions to the use of contrast agents (dizziness, nausea, vomiting, itching, urticaria, burning sensation, blood pressure drop, heartbeat abnormality, dyspnea, kidney disease, acute renal failure, etc.)
- congestive changes in the abdominal muscles on MR examination

(Limited to cases where there is a scar on the abdomen and the procedure is performed after applying a scar patch.)

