**15.6.3. Reporting Serious Adverse Events/Medical Device Reactions**

The investigator shall record all serious adverse events/adverse medical device reactions that occurred during the clinical trial period on a serious adverse event record sheet, and report it to the sponsor within 24 hours regardless of the relationship with the investigational medical device. In this case, in order to protect the ity of the subject's identity, the subject identification code is used in place of the subject's personal information.

In addition, events that suggest significant risks, contraindications, side effects, and precautions that the investigator considers serious or that may be related to the use of investigational medical device are also recorded as serious adverse events/adverse medical device reactions and reported immediately to the sponsor.

When reporting a death case, the investigator must submit additional information such as an autopsy report (applicable only when an autopsy has been performed) and a death certificate to the sponsor and the IRB.

The sponsor shall report serious and unexpected adverse events (including adverse medical device reactions, serious adverse events/adverse medical device reactions) to the Institutional Review Board and the Minister of Food and Drug Safety as soon as possible within the period specified in each of the following subparagraphs.

1. For death or life-threatening cases, the principal investigator must report additional information within 7 days of receiving the report or becoming aware this fact, and in this case, detailed information must be reported within 8 days from the date of the initial report.
2. Any other serious or unexpected adverse events should be reported within 15 days of the principal investigator receiving the report or becoming aware this fact.
3. When a sponsor wishes to report an adverse medical device reaction to the Minister of Food and Drug Safety in accordance with 1) above, it must be submitted in the adverse medical device reaction report according to Form of Attachment No. 36 of the KGCP.

In relation to reporting serious adverse events and adverse medical device reactions, additional safety information should be periodically reported until the relevant adverse reaction is resolved (disappearance of the relevant adverse reaction or lost to follow-up, etc.).

ALPINION Medical Systems Co., Ltd. 37/45

Protocol No. APM-03 Version 1.10/Date 20180103

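### The SAE and AE definitions contradict each other on causality and on scope, so the safety tables are not uniquely defined and may undercount or differ between the two sites

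*Protocol*

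**What the plan says.** **Serious events.** Protocol 15.2 gives one joint definition for the serious adverse event and the serious device reaction. Such an event "refers to a case that falls under the following among the adverse reactions caused by medical devices used in clinical trials", and four seriousness criteria follow. Section 15.6.3 has the investigator record all of these events over the trial period and "report it to the sponsor within 24 hours regardless of the relationship with the investigational medical device". It adds a catch-all: events suggesting significant risks or side effects "that the investigator considers serious or that may be related to the use of investigational medical device" are also recorded as serious.

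**Adverse events.** Section 15.1 defines an AE as "any undesirable and unintended signs (signs, e.g., abnormalities in laboratory test values), symptoms, and diseases occurring in subjects during clinical trials", and adds that "it does not necessarily have to have a causal relationship with the investigational medical device". Section 12.3.2, repeated in 15.4, says that in this trial "adverse events are all undesirable medical findings that cause symptoms not observed before the start of the clinical trial". Both sections then widen this. In the words of 15.4, "Expected side effects are also classified as adverse events", and the list of those effects is in 15.5.1.

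**Use of the definitions.** The safety endpoint in 12.3.1 is all adverse events during the trial. Section 13.3.4 tabulates AEs, device reactions and SAEs as separate categories. Section 16.8 treats clinically meaningful laboratory abnormalities as adverse events.

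**The concern.** Safety is a stated objective of this trial, which is meant to support approval of a new indication. Its safety evidence is the set of tables in 13.3.4, and the events entering them are fixed by the definitions sites use when they record. If two sections give different answers for the same event, the table has no single correct count, and two sites reading the same protocol in good faith can record differently. An analysis plan can choose how to tabulate what was recorded, but it cannot recover an event that a site left out because one section said it did not qualify.

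On causality, the gap matters because subjects are exposed to more than the device. They receive sedation before the procedure (11.6.3) and contrast agents for MRI (11.5), and 11.6.2 itself refers to MR contrast agents as drugs. A serious reaction to either is not, on a plain reading, one caused by a medical device.

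On scope, the trial is planned to produce findings without symptoms: laboratory tests are repeated at Visit 3 and MRI after the procedure and at Visits 3 and 4.

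**Working it through.** No arithmetic applies. The protocol states no expected AE or SAE rate and no safety hypothesis. The check is to take types of event and classify each under the competing sections as written.

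**Step 1: causality of SAEs (15.2 against 15.6.3)**

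| Event meeting a seriousness criterion | SAE under 15.2? | Recorded and reported as an SAE under 15.6.3? |
| --- | --- | --- |
| Caused by the device | Yes | Yes |
| Reaction to sedation | No, a drug caused it | Yes, on the relationship-free rule or the catch-all |
| Reaction to contrast agent | No, a drug caused it | Yes, same reason |
| Unrelated illness | No | Yes, same reason |

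If 15.2 is taken literally, an SAE unrelated to the device cannot exist, and the instruction in 15.6.3 to disregard relationship has nothing to act on. Two other sections presuppose that such events exist. The causality scale in 15.3.2 runs down to a category of definite non-relationship, and 13.3.4 lists SAEs apart from device reactions.

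**Step 2: scope of AEs (15.1 against 12.3.2 and 15.4)**

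| Event | AE under 15.1? | AE under 12.3.2/15.4? |
| --- | --- | --- |
| New symptom | Yes | Yes |
| Increased vaginal bleeding, pain, cramping, urination problems | Yes | Yes, through the expected list |
| Contrast hypersensitivity | Yes | Yes, through the list ("Hypersensitivity reactions to the use of contrast agents") |
| Worsening of a pre-existing symptom not on the list | Arguably yes, though worsening is not named | No |
| Laboratory abnormality without symptoms, not on the list | Yes, named explicitly | No |
| Imaging finding without symptoms, not on the list | Yes, as a sign | No |

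The list does cover some findings that could be symptom-free: internal thermal damage, organ damage and, for scar-patch cases only, one MR change in the abdominal muscles. The remaining gap is findings and worsening outside the list.

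**Step 3: does a cross-reference settle it?** Section 12.3.2 relies on Section 15 for its definitions, but Section 15 holds both versions (15.1 and 15.4). The AE note to the schedule in 11.5 sends the reader to Section 16, which deals with subject protection and contains no AE definition. Neither pointer tells a site which rule governs.

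**Step 4: bounds.** If sites follow 15.1 and 15.6.3, nothing is lost. If they follow 15.2 and 15.4 literally, the tables lose every serious event judged not caused by the device, every unlisted worsening and every unlisted symptom-free finding. Nothing in the protocol places the result between these ends.

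**The case against.** The strongest reply is that the broad rules are already in the protocol and are the ones sites act on. Section 15.6.3 is the operative reporting rule, and its catch-all reaches events the investigator considers serious. Section 12.3.1 takes all adverse events as the endpoint, and 16.8 counts meaningful laboratory abnormalities. Section 13.3.4 also summarises vital signs and blood tests as safety data in their own right, so a laboratory value stays visible even if it is never called an AE.

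Much of this stands, and it rules out several stronger readings:

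- A reader might infer that the safety counts will be too low. The documents do not show that. Sites following the broad rules would record everything, so the supportable statement is that counts may be too low or may differ between sites.
- A reader might infer that worsening of the symptoms typical of this disease goes uncounted. Most of it does not: pain, drug-resistant pain, cramping, increased bleeding and urination disorders are on the expected list, and 12.3.2 and 15.4 both bring that list in.
- A reader might size the gap by counting sedations and contrast MRI sessions, or by the shift in an upper confidence limit if one serious event were omitted. The first counts exposures, not lost events. The second assumes the omission it is meant to show, and no safety threshold in the protocol turns on such a limit.
- The schedule ticks AE collection only from Visit 2, although contrast MRI is done at screening. Since the safety set is treated subjects only, this is a secondary design preference and not part of the contradiction.

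The reply does not remove the conflict. A broad rule in one section does not repair a narrow definition in another when nothing says which prevails, and 15.2 is the section headed as the SAE definition.

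**Conclusion.** The point holds as an inconsistency in the definitions. Section 15.2 contradicts 15.6.3 on whether an SAE must be caused by the device, and 12.3.2 and 15.4 contradict 15.1 and 16.8 on what counts as an AE. The SAE and AE tables in 13.3.4 are therefore not uniquely defined.

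The exposed events are serious events judged not caused by the device, unlisted worsening of pre-existing symptoms, and unlisted findings without symptoms. The size of any undercount cannot be derived from the protocol and may be zero. This conclusion assumes only that a site could reasonably apply 15.2 or 15.4 as written. It does not touch the primary efficacy test, the success criterion or the sample size.

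**What to change.** 1. In 15.2, define an SAE as any adverse event, as defined in 15.1, that meets one of the four seriousness criteria, whatever its cause. Define the serious device reaction as the subset for which a causal relationship with the device cannot be excluded. This makes 15.2 agree with 15.6.3, 15.3.2 and 13.3.4.
2. In 12.3.2 and 15.4, replace the condition that symptoms be new since the start of the trial with the 15.1 definition, and state that worsening of a pre-existing sign or symptom counts as an adverse event. Section 15.1 does not name worsening, so this needs saying. The sentence on expected side effects can stay.
3. While amending, correct the AE note to the schedule in 11.5 so that it points to Section 15.

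The cost is wording in a few sections, and sites will record slightly more events. The change should be made before data collection, since events never recorded cannot be restored at analysis.

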**15.3. Assessment of Adverse Events**

**15.3.1. Severity Assessment**

If an adverse event occurs, it should be reported according to the following severity assessment criteria.

① Mild

Cases that do not interfere with the subject's normal daily life (function), cause minimal discomfort, and are easily tolerated by the subject

② Moderate

In case of causing discomfort that significantly interferes with the normal daily life (function) of the subject ③ Severe

When the subject's normal daily life (function) is impossible

**15.3.2. Assessment of Causality with Investigational Medical Device**

When an adverse event occurs, the investigator assesses whether it is related to the investigational medical device according to the following criteria, and the investigator's opinion is described.

ALPINION Medical Systems Co., Ltd. 34/45

Protocol No. APM-03 Version 1.10/Date 20180103

① Definite

② Probable

③ Possible

④ Possibly not

⑤ Definitely not

⑥ Unknown

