**11.6.2. Clinical Trial Procedures**

1. **Screening <Visit 1>**

Patients diagnosed with adenomyosis through MR or US imaging are referred to this clinical trial by a gynecologist or interventional radiology department. They will be enrolled in this clinical trial if they satisfy all of the inclusion/exclusion criteria and sign the written consent form voluntarily after being given sufficient explanation on this study.

At the Screening visit, in addition to the inclusion/exclusion criteria, demographic survey, vital signs, physical examination, past medical history, blood tests, pregnancy tests, ECGs, MRIs, ultrasound tests, and questionnaires are used to evaluate the degree of menstrual pain and menorrhagia. The ability to communicate with the investigator and willingness to comply with the clinical trial will also be assessed during the Screening period.

Pre-procedure MRI

An intravenous catheter may be inserted prior to the procedure in order to obtain MRI images before and after using the contrast medium as well as the T1- and T2-weighted images for 3 orthogonal planes, and to administer drugs such as MR contrast agents and weak stabilizers.

Pre-procedure MRI is the final step in determining inclusion/exclusion. For post-treatment MR imaging, a contrast medium commonly used for gynecological imaging in hospitals will be used according to the product manual. (Follow the standard procedure of the hospital)

ALPINION Medical Systems Co., Ltd. 24/45

[figure not shown]

[figure not shown]

Protocol No. APM-03 Version 1.10/Date 20180103

[figure not shown]

1. **Procedure day <Visit 2>**

- HIFU Treatment Protocol

The US-guided HIFU procedure is expected to take 2 to 4 hours, including recovery time (1 to 2 hours) after the procedure is completed. The duration for which the subject remains immobile should be limited to about 3 hours to reduce the risk of deep vein thrombosis (DVT).

- Preparation

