**11.6.3. Concomitant Therapy**

Drugs that may affect the treatment of adenomyosis (see Contraindicated Drugs below) or alternative treatments are prohibited. All drugs already being taken due to underlying diseases are recorded at the time of Screening. Only the drugs added thereafter are recorded in the CRF. If any of the above contraindicated drugs or alternative treatments were received during the clinical trial period, they will be withdrawn from the study and the reason for withdrawal should be recorded.

However, even if it is a contraindicated drug, if a one-time administration is necessary regardless of this study, it can be used within the extent that does not affect the procedure result at the discretion of the investigator and the related information is recorded in the concomitant drugs section of the CRF.

Subjects are administered midazolam and fentanyl for sedation prior to the procedure. The dosage of midazolam and fentanyl is determined by the investigator in consideration of the age and clinical condition of the subject, but generally midazolam 3mg/3ml or 5mg/5ml, and fentanyl 100mcg/2ml are administered. At the discretion of the investigator, analgesics, sedatives and local anesthetics may be administered according to the standard procedure of the institution in consideration of the subject's condition.

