**13.3.4. Safety Analysis**

Safety assessment is performed based on all adverse reactions, vital signs, blood tests, etc. collected from the subject.

All the above safety variable data collected up to 3 months after the procedure are presented for each time point at which each safety endpoint was measured and for each subject, and summary statistics are presented. Adverse events collected from subjects will be coded using MedDRA. Adverse events, adverse medical device reactions, SAEs, deaths, adverse events that resulted in clinical trial discontinuation, and the number of subjects who exhibited each adverse reaction will be summarized by the system organ class (SOC), preferred term (PT) and maximum severity.

1. **Clinical Trial Discontinuation and Dropout Criteria**

If participation is withdrawn after consent to participate in the clinical trial, or if participation in the clinical trial is judged to affect the safety of the subject under the judgment of the principal investigator, participation in the clinical trial may be suspended or the subject may be withdrawn from participation.

ALPINION Medical Systems Co., Ltd. 32/45

Protocol No. APM-03 Version 1.10/Date 20180103

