**15.6.2. Recording Expected Adverse Events**

When an expected adverse event occurs, the investigator records the following in the CRF.

- Name of adverse event
- Date of onset and resolution
- Severity
- Causal relationship with the investigational medical device
- Treatment details and outcome

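### Causality is collected only against the device, so harms of the sedation, contrast MRI, bladder adjustment and immobility that accompany treatment may be missing from, or inconsistently counted in, the device-reaction table

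*Protocol*

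**What the plan says.** Protocol 15.3.2 has one causality question. When an adverse event occurs, "the investigator assesses whether it is related to the investigational medical device according to the following criteria". The grades run from Definite to Definitely not, with Unknown as a sixth. None is defined, and no rule says which count as related. The investigator's opinion is also to be described.

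The CRF list in 15.6.2, which is written for expected events, carries the same single item: "Causal relationship with the investigational medical device". Section 15.1 defines an adverse device effect as a reaction caused by the device, where "a causal relationship with the investigational medical device cannot be excluded". An adverse event is wider, since "it does not necessarily have to have a causal relationship with the investigational medical device".

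The treatment course is more than the device:

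- 11.6.3: "Subjects are administered midazolam and fentanyl for sedation prior to the procedure".
- 11.5 (MRI note): contrast-enhanced MRI is taken immediately after the procedure, as well as at screening and follow-up.
- 11.6.2 (Preparation): bladder volume is adjusted on the day, if necessary.
- 11.6.2 (HIFU Treatment Protocol): the time for which the woman lies still "should be limited to about 3 hours to reduce the risk of deep vein thrombosis (DVT").
- 15.5.1: the expected events include "Hypersensitivity reactions to the use of contrast agents".

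Section 13.3.4 plans summaries of "Adverse events, adverse medical device reactions, SAEs, deaths, adverse events that resulted in clinical trial discontinuation", by system organ class, preferred term and maximum severity. No table of procedure-related events is planned.

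**The concern.** The section on the objective of the trial asks for the safety of adenomyosis ablation performed with this device. That is a treatment, and a woman who has it also has the sedation, the scan and the period of immobility. Section 11.1 gives a single-arm design, so no control group shows how much of the adverse event total is background over three months. Recorded attribution is then a main tool for separating treatment harm from background, alongside timing and event type.

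The protocol collects attribution for one component only. If the procedure is not asked about at the time, it cannot be recovered later in a consistent form. An analysis plan can add a table, but it cannot fill one from a field that the CRF does not have.

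**Working it through.** The protocol gives no figure on this point to reproduce, so the check sets its sections side by side.

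**1. Is relation to the procedure asked anywhere?** No. 15.3.2, 15.6.2 and the adverse device effect definition in 15.1 all refer to the device alone. The protocol does draw the distinction elsewhere: the indemnification policy in 16.4 covers injury from the device or from a clinical procedure.

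**2. Where would a procedural harm be counted?** Take an event whose evident cause is the sedation, the procedure-day contrast agent or the immobility.

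- Read literally, 15.3.2 asks about the device, so a low grade is a reasonable answer and the event stays out of the device-reaction table.
- Read through 15.1, a link that cannot be excluded is enough, so Possible is also defensible and the event may go in.
- With no grade definitions and no stated cut, both readings comply. The two sites can differ on like events.

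**3. Does the table of all adverse events solve this?** It contains the events but not their source. In 15.5.1 nausea and vomiting are listed in their own right and again as signs of a contrast reaction, so one preferred term can have more than one origin. Deep vein thrombosis, named as a risk in 11.6.2, is not in the expected list. Neither is any event described there as due to sedation.

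**4. Serious events.** 15.2 defines a serious event as falling among reactions caused by medical devices. 15.6.3 has serious events reported to the sponsor within 24 hours whatever their relationship to the device, and also brings in events that the investigator considers serious. A serious sedation event judged not due to the device is outside 15.2 and inside 15.6.3. Which of the two governs the SAE table in 13.3.4 is not stated.

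**5. Size.** Let N be the women treated, d those with at least one device-related event, and q those whose only treatment-related event is procedural.

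- Device-related rate: d/N
- Device-or-procedure rate: (d + q)/N
- Difference: q/N

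With all 80 planned women treated, the difference is q/80, or 1.25 percentage points per woman. The possible range runs from 0 (q = 0) to (80 − d)/80. The protocol gives neither d nor q, nor any event rate for sedation, contrast or immobility, so no value inside that range can be derived.

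**The case against.** The strongest reply is that nothing is hidden. The safety endpoint in 12.3.1 is all adverse events, with no filter on relatedness. Expected side effects count as adverse events (12.3.2, 15.4), and contrast reactions and urinary tract infection are listed by name. 13.3.4 tabulates all events and presents safety data by time point and by subject. Onset dates are recorded and events are checked on the procedure day, so an acute reaction to sedation or contrast would often be recognisable in a trial of 80. The device-reaction table does not claim to count procedural harm. The described opinion in 15.3.2 may also name the procedure as the cause.

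Most of this stands, and it limits the point. A reader might infer that harms of sedation, contrast and immobility are classed as unrelated, and that the tables therefore understate the harm of the procedure. The documents do not support that. No rule assigns those harms a grade, Possible and Unknown are available, and 15.1 takes in links that cannot be excluded. Omission is one permitted outcome, not a fixed one.

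Some components also need care. Bladder adjustment is done only if necessary, ultrasound contrast is optional (11.5), and the Month 1 and Month 3 scans are follow-up imaging, not treatment.

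The reply does not remove the gap itself. Free-text opinion is not a coded field, timing helps less for a delayed event such as thrombosis, and no planned output counts the women harmed by having the treatment. The layout of tables can be left to an analysis plan, but collection of the item cannot.

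**Conclusion.** The point holds in a limited form. Causality is collected against the device only, on an undefined scale with no procedure-related category. Harms of the accompanying steps may be left out of the device-reaction table or enter it inconsistently, and would then appear only in the all-event table, without attribution.

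The size of any understatement is unknown. It is 1.25 percentage points for each woman affected if 80 are treated, and it may be zero. This rests on investigators answering the question as worded, at least some of the time. The primary efficacy analysis is not affected, and the all-event data remain complete. The conflict between 15.2 and 15.6.3 adds to the problem, because it leaves open whether a serious procedural event counts as an SAE. Overall this is a cheap improvement that would make the safety result more informative about the treatment named in the objective.

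**What to change.** - **15.3.2 and 15.6.2:** add a second causality item on the same six-grade scale, for example: related to the treatment procedure (sedation, procedure-day contrast agents, bladder-volume adjustment, positioning or immobility). Keep it separate from the Month 1 and Month 3 follow-up imaging, so that harm from trial scans is not counted as harm from treatment.
- **15.3.2:** state which grades count as related, including how Unknown is handled.
- **13.3.4:** tabulate device-related and device-or-procedure-related adverse events and SAEs by system organ class, preferred term and maximum severity.
- **15.2 and 15.6.3:** reconcile the SAE definition with the reporting rule, so that serious procedure-related events are counted as SAEs.

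The cost is one CRF field, one table and a short text amendment. The reported related-event rate may look slightly less favourable.
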